### Data management

2.11

DepFuD's documents are stored at KUH, Department of Psychiatry, in the password‐protected safe disk storage system provided by the KUH information administration and in the University of Eastern Finland (UEF) password‐protected personal disk storage system. Biological samples are stored in the sample freezers at KUH. Documents and biological samples are kept for 20 years, after which biological samples are physically destroyed and papers are destroyed by shredding. Data are stored and processed with Microsoft Excel (Microsoft Corporation, Redmond, WA) and IBM SPSS (IBM Corp., Armonk, NY) software. Data collected by paper forms and data obtained from blood samples are entered into the database by the study nurse and research assistants. The study questionnaires are checked for unanswered items, which, if needed, are completed with assistance from the study nurse. Range checks are performed during analyses, and identified errors are corrected, if possible. Researchers and collaborators are only provided with data that do not contain personal identification information. Data are treated as pseudo‐anonymous, with each subject assigned an identification number for the DepFuD project. The study's data are not attached to medical records, except for Structured Clinical Interviews for DSM‐IV (SCID‐I) and (SCID‐II) diagnoses. DepFuD data are not released outside the research group without a separate written data usage agreement between the research group and the external researcher. Biological samples can be analyzed anonymously also outside of Finland (countries of European Union (EU) and other countries where legislation guarantees adequate privacy protection).

### Special considerations related to genetic research

2.12

Subjects received a separate information and consent form for taking a DNA sample and using it for research after reading the plain language statement. DNA samples are stored frozen at KUH Mental Health and Wellbeing for up to 20 years, after which further storage and analyses require a new Research Ethics Committee permit. DNA samples and other biological samples are disposed of as hazardous waste by incineration, preventing outsider access to identification information. The data obtained through the DNA sample are processed and examined only as pseudo‐anonymous coded materials. Thus, individual genetic results will not be shared with the subject or anyone else. The genetic information generated by DepFuD will be primarily used for scientific research. If the study also generates applied information suitable for therapeutic or diagnostic purposes in cooperation with industry, the operation will take place in accordance with the regulations of KUH. The DNA samples are examined for genetic characteristics that may be linked to depression or VD metabolism. The significance of some genetic characteristics is currently unknown, but future genetic research results may guide the final examinations of the stored DNA samples.

### Statistical methods

2.13

Statistical analyses will be conducted with current versions of appropriate mainline statistical software: IBM SPSS Statistics for Windows (IBM Corp., Armonk, NY), R with suitable packages (R Foundation for Statistical Computing, Vienna, Austria), Stata Statistical Software (StataCorp, TX), or SAS software suite (SAS Institute Inc., NC). Continuous baseline and longitudinal data will be expressed as means with SDs or as medians with inter‐quartile ranges (IQRs)/ranges, whereas categorical variables will be expressed as proportions. Confidence intervals (95% CIs) will be calculated for risk ratios, for risk differences for categorical variables, and for mean differences for continuous variables. Baseline data will be analyzed cross‐sectionally for factors correlated with symptoms of depression. In cross‐sectional and longitudinal analyses e.g. analysis of variance (ANOVA), logistic or linear regression analysis, mixed models, and, if necessary, Cox regression analysis based on registry data will be utilized.

For the primary outcome, an intention‐to‐treat analysis will be performed for all randomized subjects who attended to all study visits during the intervention and completed study questionnaire without missing primary outcome data. RCT participants, who reported using over 10 μg (400 IU) of VD supplement outside the study almost daily at baseline or at 6 months despite prohibition, will be excluded from intervention analyses. Additional comparative analyses can be conducted with and without these participants. Subgroup analyses for the intervention data will be based on factors like baseline VD status, age, sex, and body mass index (BMI). If multiple effect estimates are generated for a specific outcome measurement, all estimates will be reported. Follow‐up analyses will consider background characteristics and secondary outcomes. The randomness and impact of missing data will be evaluated for primary and secondary outcome analyses, and imputation methods and sensitivity analyses may be used for specific subgroup analyses. KUH and UEF statisticians will be consulted for more advanced statistical models.

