### Data collection, management, and analysis

2.10

Study data are collected through self‐administered paper or online questionnaires, clinical interviews, health examinations, and blood samples. Subjects were also asked for their consent to the use of their medical record data for the study. See Figure 1 for the schedule for the data collection and for the complete list of used clinical scales and measures, clinical interviews, health examinations, and analyzed biomarkers. There are no specific plans to minimize loss to follow‐up. Separate data were not collected from those who refused to participate in the study, and DepFuD data collection ends if subject discontinues participation.

The clinical scales, measures, and interviews used are internationally validated and established. A description of the study instruments along with their expected reliability and validity is presented in Table 2. Preexisting Finnish translations are used. Subjects had the opportunity to fill out the study questionnaire at their psychiatric care unit at baseline, 3, and 6 months. At 18 months, subjects received mailed questionnaires with an information letter and a return envelope. At the 6‐year follow‐up, subjects can choose whether to fill out either the mailed questionnaire or an online questionnaire. The study nurse conducted health examinations at baseline, 3 months, 6 months, and 18 months, measuring weight, height, waist circumference, hand grip strength, and blood pressure. Blood samples were taken at these same intervals.

**TABLE 2 fsn34417-tbl-0002:** The description of the DepFuD study instruments along with their expected reliability and validity.

Instrument	Description
Clinical interviews	
Montgomery–Åsberg Depression Rating Scale (MADRS)	A 10‐item diagnostic questionnaire with adequate inter‐rater reliability and validity to measure the severity of depressive symptoms in patients with mood disorders. Developed to be sensitive to change in depressive symptoms and to differentiate between responders and nonresponders to antidepressant treatment. Each item is rated 0–6 and items are summed (overall score range 0–60, higher score indicating more severe depression) (Montgomery & Åsberg, 1979). A score decrease to ≤10 is defined as a remission and a score decrease by 50% from baseline is defined as a response to treatment (Zimmerman et al., 2004).

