### Baseline characteristics

5.1

A total of 319 patients (302 from Kuopio, 16 from Jyväskylä, and 1 from Mikkeli) were enrolled and gave informed consent. Data from baseline assessments (self‐administered background information, self‐administered clinical scales and measures, health examinations, clinical interviews, or blood samples) are available from a total of 319 subjects. Two hundred eighty‐one subjects were assigned to the RCT and 38 chose to participate in the follow‐up study. For the RCT, subjects were randomized and double‐blinded to supplement groups 1 (142 subjects) and 2 (139 subjects).

Table 3 presents the baseline characteristics of the sample. Analyses were performed with IBM SPSS Statistics for Windows version 27. The median age was 31 years (IQR 15, range: 20–61) and 74% of the subjects were women. The most common marital status was single (50%) and 37% of the subjects were currently in a relationship. The average of full‐time schooling during life was 14.7 (SD 3.1, range: 2–26), and the highest level of completed education was most commonly middle school and vocational degree (38%) or high school and some another degree (24%). Fourteen percent of the subjects reported a completed academic degree. Forty percent of the subjects were not currently working due to various reasons, including sick leave or studying. Twenty percent of the subjects were employed full‐time, 23% were unemployed, and the rest were on different forms of pension.

**TABLE 3 fsn34417-tbl-0003:** Baseline characteristics of the DepFuD participants (*n* = 319) reported as frequencies, mean (M) with standard deviation (SD), or median (Md) for non‐normally distributed data.

Background information	
Age (years), Md (25th percentile, 75th percentile)	31 (25, 40), min–max: 20–61 (missing: *n* = 3)
Men	81
Women (frequency)	236 (missing: *n* = 2)
Single	160
In relationship	116
Separated or divorced	40
Widowed (frequency)	1 (missing: *n* = 2)
Education	
Part of public or elementary school	1
Public school or part of middle school	9
Middle school or part of high school	20
Middle school and vocational education	121
High school degree	47
High school and some another degree	75
Academic degree (frequency)	44 (missing: *n* = 2)
Studied full‐time (years), M (SD)	14.7 (3.1), min–max: 2–26 (missing: *n* = 4)
Full‐time work	63
Shortened working week	10
Part‐time work	28
Unemployed	72
Unemployment pension	1
Part‐time pension	2
Disability pension	12
Employment pension	1

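### The primary analysis is labelled intention-to-treat but defined as a completers set with a per-protocol-type exclusion, and no estimate in all 281 randomised is committed to

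*Protocol article*

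**What the plan says.** Section 2.13 (Statistical methods) announces an intention-to-treat analysis of the primary outcome and says it will be "performed for all randomized subjects who attended to all study visits during the intervention and completed study questionnaire without missing primary outcome data". The next sentence adds a second filter. Participants who took more than 10 μg of a "VD supplement outside the study almost daily at baseline or at 6 months despite prohibition" "will be excluded from intervention analyses". Bringing them back is optional: "Additional comparative analyses can be conducted with and without these participants".

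On missing data, the same section commits to evaluating its randomness and impact for the primary and secondary outcomes. It then narrows the tools: "imputation methods and sensitivity analyses may be used for specific subgroup analyses". Mixed models appear only in a general list of example methods and are not tied to the primary outcome.

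The primary outcome (Section 2.3.1) is the between-group difference in MADRS change from baseline to 6 months. Intervention visits are at 3 and 6 months (Section 2.8). Section 2.10 states that there are no specific plans to limit loss to follow-up and that "DepFuD data collection ends if subject discontinues participation".

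**The concern.** Intention-to-treat means that everyone randomised is analysed in the arm they were allocated to. Here, membership of the set depends on things that happen after randomisation: attending every visit, completing the questionnaire, having the outcome observed, and what is reported about supplements at 6 months. If any of these relates to both arm and outcome, the two groups being compared are no longer the two groups that were randomised.

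The rule is also stricter than a complete-case rule. Someone with MADRS at baseline and 6 months who missed month 3 has an observed primary outcome and is still removed. Table 2 lists MADRS among the clinical interviews, apart from the self-report scales, so an incomplete questionnaire need not mean a missing MADRS.

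At stake are the meaning of the main result and its label. Readers of the report will take intention-to-treat to mean that the randomised comparison was preserved.

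**Working it through.** **Inputs.** Randomised: 142 + 139 = 281 (Section 5.1). Expected attrition 25%, target difference 4 MADRS points, SD 12, alpha 0.05, power 0.90 (Section 2.5). RCT participants with near-daily off-protocol vitamin D use at baseline: 19 (Section 5.1). Baseline MADRS missing: 0 (Table 3, whole sample of 319). Two-sided testing is stated for the 2015 calculation and assumed for 2019.

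**1. The plan's own figure.** A two-sided two-sample t-test with difference 4 and SD 12 has power 0.8999 with 190 per group and 0.9013 with 191. The stated 191 per group (382 in total) is reproduced.

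**2. Size of the analysed set.**
- Attrition only: 281 × 0.75 = 210.75, about 211. Left out: 281 × 0.25 = 70.25, about 70.
- Attrition plus baseline supplement users, with 25% attrition among the rest: (281 − 19) × 0.75 = 196.5, about 197. Left out: 84.5, or 84.5/281 = 30%.
- The number reporting outside use at 6 months is not given, so the second figure could be lower.

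**3. Power for 4 points with SD 12.** 0.795 with all 281 observed, 0.673 at about 211, 0.642 at about 197. An analysis of all randomised with 25% of outcomes missing would lie between 0.673 and 0.795.

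**4. Possible bias (assumed values).** Let arm a have dropout proportion q_a and completer mean c_a, and let dropouts end g points worse than completers in both arms. The all-randomised mean is c_a + q_a × g. The completers' difference therefore departs from the all-randomised difference by |q_1 − q_2| × g.
- Equal attrition: 0 × g = 0.
- Imbalance 0.10, gap 5 to 8: 0.10 × 5 = 0.5; 0.10 × 8 = 0.8. Against 4 points: 0.5/4 = 12.5%; 0.8/4 = 20%.
- Wider range, imbalance 0.05 to 0.15 and gap 2 to 6: 0.05 × 2 = 0.1 up to 0.15 × 6 = 0.9.
- Unequal gaps matter even with equal attrition. With 25% dropout in each arm, an effect of 4 in completers and 0 in dropouts gives 0.75 × 4 + 0.25 × 0 = 3.0 for all randomised.

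**5. Observed outcomes discarded (assumed share).** If a further 5% of those randomised (0.05 × 281 = 14) have both MADRS values but miss a visit or the questionnaire, the analysed fraction falls from 75% to 70%. The confidence interval widens by √(0.75/0.70) = 1.035, about 3.5%.

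**6. The two parts of the supplement rule.** Randomisation followed the baseline examinations (Section 2.7). Use reported at baseline is therefore a pre-randomisation characteristic, and removing those people narrows the population without in itself unbalancing the arms. Use reported at 6 months comes after randomisation. Neither removal fits an intention-to-treat label.

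**The case against.** The plan does not ignore missing data. It commits to evaluating its impact on the primary outcome, says that all effect estimates generated will be reported, and names mixed models among its methods. The details of that evaluation could properly sit in an analysis plan that is not shown. This stands, and it rules out saying that nothing in the plan addresses the problem. It does not supply an all-randomised estimate: the article itself fixes the primary set, and its only words on imputation and sensitivity analysis make them optional and point to subgroups.

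A reader might infer that the definition costs the trial about 70 people. The documents do not support that. Participants lost before 6 months have no 6-month MADRS under any definition. Beyond them, the rule removes those with both values who missed a visit or questionnaire, plus the supplement users. The 25% is a planning allowance, not a result.

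A reader might also infer that the result is biased by 0.5-0.8 points. Nothing in the documents points to a 10-percentage-point imbalance: the tablets look identical, the trial is double-blind, and no unexpected harms were reported (Sections 2.9 and 2.14.2). Nor is the 1.6-1.9-point change cited in Section 2.5 the right yardstick, because the protocol sets its own threshold of 4 points for this trial.

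The questionnaire condition may exclude few people. The study nurse helps to complete unanswered items where needed (Section 2.11), and Table 2 describes MADRS itself as a questionnaire, so the wording leaves some room. The visit condition has no such softening.

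**Conclusion.** The point holds as a fault in the stated definition and label. The primary analysis is a completers analysis with a per-protocol-type exclusion. It can discard observed primary outcomes, and no primary or sensitivity estimate in all 281 randomised is committed to. This rests on the wording of Section 2.13 and needs no assumption about dropout.

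The size of the set, about 211 or about 197 of 281, rests on the protocol's planned 25% attrition, since actual completion is not reported. The direction and size of any bias cannot be determined. The 0.5-0.8 points illustrate one assumed pattern; equal attrition with equal gaps gives zero. The documents support a claim of possible bias, not of demonstrated bias.

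**What to change.** Define the primary set as all 281 randomised, analysed as allocated. Remove the attendance, questionnaire and outside-supplement conditions from the primary analysis. All three have to go: if the supplement sentence stays, the text will still contradict the intention-to-treat label.

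For missing 6-month MADRS, use a likelihood-based repeated-measures model if MADRS was rated at 3 months (the schedule is in Figure 1, which was not available for this review). Otherwise use multiple imputation with arm, baseline MADRS and the 3-month data that were collected; Section 2.10 places questionnaires, health examinations and blood samples at that visit. Commit to a delta-adjusted, missing-not-at-random sensitivity analysis of the primary outcome. Keep the present set, with its supplement exclusion, as a supplementary analysis labelled completers/per-protocol.

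RCT data collection ended in December 2020 (Section 2.4), so the change should be dated and should state whether the allocation code had been opened.

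The cost is a little more analysis work and reliance on a stated missing-at-random assumption, which the sensitivity analysis tests. No new data are needed.

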### Monitoring

2.14

#### Data monitoring

2.14.1

This study does not have external data monitoring committee or preplanned interim analyses for early stopping (either for futility or for positive efficacy). The absence of a data monitoring committee can be justified with a relatively short intervention duration with a well‐characterized, safe, and nonexperimental drug (VD; cholecalciferol). In Finland, the Research Ethics Committee does not require a data monitoring committee in dietary supplement interventions. The condition of the subjects in our sample of adult outpatients with nonpsychotic depression is noncritical, and the potential harm for subjects is expected to be minimal (see Section 2.14.2 Harms for stopping guidelines).

#### Harms

2.14.2

Potential short‐term or long‐term health risks from the intervention are unlikely with the VD amounts used (10 and 100 μg/day) (European Food Safety Authority, 2016). The small tablets, sweetened with sorbitol and xylitol, were easy to consume and daily doses were not expected to have laxative effects. Research visits, giving blood samples, and filling the questionnaires cause burden to the participants. In addition, during the VD intervention, the subject had to remember to take VD supplement daily. Serum calcidiol, calcium, and parathyroid hormone concentrations were checked at baseline, 3, and 6 months to detect hypercalcemia and possible need for discontinuation. Subjects' clinical status was monitored as usual by their attending physician, and they were advised to consult their attending physician if they suspected health issues due to VD use. During the VD intervention, no unexpected harms were reported to the study group.

#### Auditing

2.14.3

None.

## ETHICS AND DISSEMINATION

3

### Research ethics approval

3.1

The Medical Research Ethics Committee of Wellbeing Services County of North Savo, KUH, approved the study (ethics approval and consent number 39/2015). The study conforms to the Declaration of Helsinki (World Medical Association, 2022).

### Protocol amendments

3.2

Protocol modifications will be submitted to the Regional Research Ethics Committee and public ClinicalTrials.gov record will be updated after protocol modifications. The updated sample size calculation and target sample size were accepted by the Research Ethics Committee in June 2020 (see Section 2.5 Sample size). In contrast to original plan, the randomization was not done separately for women and men. The time point of the final data collection is extended from original 5 to 6  years. Originally, the final follow‐up included blood samples, health examination, and clinical interviews. Due to a lack of funding, only questionnaire data will be collected at 6 years.

### Consent or assent

3.3

The personnel at the recruitment sites obtained informed consent from the potential study participants during the first doctor's appointment. Written informed consents were then submitted to the study nurse. For more details, see Section 2.6 Recruitment and 2.11 Data management.

### Confidentiality

3.4

See Section 2.11 Data management.

### Access to data

3.6

DepFuD group researchers, as outlined in the Research Ethics Committee documentation, have access to the final dataset. Any data required to support the protocol can be supplied on request.

### Ancillary and post‐trial care

3.7

Subjects receive standard treatment for depression during and after the intervention, with no expected harm (see Section 2.14.2 Harms) or trial participation compensation. The subjects are covered by patient injury insurance.

### Dissemination policy

3.8

Study results will be published in international, peer‐reviewed scientific journals, reported at the group level. The individual results of the study may only be reported to the subjects if the findings are deemed to have individual‐level therapeutic significance. Current biological markers of depression have only scientific significance. Future publications will be authored by DepFuD group researchers, not professional writers. Full protocol and statistical scripts for intervention analyses will be open access. Complete participant or summary level of DepFuD dataset including sensitive information will not be shared. Metadata can be published in fairdata.fi if considered necessary.

## APPENDICES

4

### Informed consent materials

4.1

The plain language statement, original informed consent form, DNA sample consent form, and questionnaire in Finnish are available from the corresponding author, TM, upon reasonable request.

### Biological specimens

4.2

See Section 2.10 Data collection, management, and analysis and 2.11 Data management.

## RESULTS

5

### Baseline characteristics

5.1

A total of 319 patients (302 from Kuopio, 16 from Jyväskylä, and 1 from Mikkeli) were enrolled and gave informed consent. Data from baseline assessments (self‐administered background information, self‐administered clinical scales and measures, health examinations, clinical interviews, or blood samples) are available from a total of 319 subjects. Two hundred eighty‐one subjects were assigned to the RCT and 38 chose to participate in the follow‐up study. For the RCT, subjects were randomized and double‐blinded to supplement groups 1 (142 subjects) and 2 (139 subjects).

Table 3 presents the baseline characteristics of the sample. Analyses were performed with IBM SPSS Statistics for Windows version 27. The median age was 31 years (IQR 15, range: 20–61) and 74% of the subjects were women. The most common marital status was single (50%) and 37% of the subjects were currently in a relationship. The average of full‐time schooling during life was 14.7 (SD 3.1, range: 2–26), and the highest level of completed education was most commonly middle school and vocational degree (38%) or high school and some another degree (24%). Fourteen percent of the subjects reported a completed academic degree. Forty percent of the subjects were not currently working due to various reasons, including sick leave or studying. Twenty percent of the subjects were employed full‐time, 23% were unemployed, and the rest were on different forms of pension.

**TABLE 3 fsn34417-tbl-0003:** Baseline characteristics of the DepFuD participants (*n* = 319) reported as frequencies, mean (M) with standard deviation (SD), or median (Md) for non‐normally distributed data.

Background information	
Age (years), Md (25th percentile, 75th percentile)	31 (25, 40), min–max: 20–61 (missing: *n* = 3)
Men	81
Women (frequency)	236 (missing: *n* = 2)
Single	160
In relationship	116
Separated or divorced	40
Widowed (frequency)	1 (missing: *n* = 2)
Education	
Part of public or elementary school	1
Public school or part of middle school	9
Middle school or part of high school	20
Middle school and vocational education	121
High school degree	47
High school and some another degree	75
Academic degree (frequency)	44 (missing: *n* = 2)
Studied full‐time (years), M (SD)	14.7 (3.1), min–max: 2–26 (missing: *n* = 4)
Full‐time work	63
Shortened working week	10
Part‐time work	28
Unemployed	72
Unemployment pension	1
Part‐time pension	2
Disability pension	12
Employment pension	1
Out of working life for other reasons (frequency)	127 (missing: *n* = 3)
Ability to work	
Able to work	40
Reduced ability to work	164
Unable to work (frequency)	113 (missing: *n* = 2)
Personal disposable income per month in euros	
≤1000	153
1001–1500	78
1501–2500	74
2501–3500	10
3501–5000	0
>5000 (frequency)	2 (missing: *n* = 2)
Perceived economic status	
Good	16
Fairly good	125
Fairly bad	117
Poor (frequency)	58 (missing: *n* = 3)
Body mass index (BMI) (kg/m^2^): Md (25th percentile, 75th percentile)	26.33 (23.19, 31.64), min–max: 16.42–62.71 (missing: *n* = 2)
Multivitamin preparation use	
Almost daily	46
Occasionally or seasonally	72
Does not use (frequency)	199 (missing: *n* = 2)
Vitamin D supplement use	Almost daily/Occasionally or seasonally/Does not use
5–10 μg/day (200–400 IU/day)	14/27/276 (missing: *n* = 2)
11–19 μg/day (440–760 IU/day)	1/5/310 (missing: *n* = 3)
20 μg/day (800 IU/day)	14/18/285 (missing: *n* = 2)
>20 μg/day (frequencies) (>800 IU/day)	28/35/254 (missing: *n* = 2)
Fatty acid preparation (e.g., fish oil capsule) use	
Almost daily	27
Occasionally or seasonally	43
Does not use (frequency)	246 (missing: *n* = 3)
Amount of night sleep (hours): M (SD)	7.52 (1.57), min–max: 3.0–12.0 (missing: *n* = 3)
Smoked regularly for at least a year during life (frequency)	153 (missing: *n* = 3)
Current smoking (within 1 month) (frequency)	116 (missing: *n* = 3)
Alcohol use	
Does not use	32
Once a month or less	113
2–4 times a month	135
2–3 times per week	35
4 times a week or more (frequency)	2 (missing: *n* = 2)
Comorbidity	
Self‐reported diagnosed psychiatric comorbidity within 12 months:	
Personality disorder	9 (missing: *n* = 2)
Anxiety disorder	93 (missing: *n* = 4)
Eating disorder	5 (missing: *n* = 2)
Alcohol addiction	9 (missing: *n* = 2)
Drug addiction (frequency)	0 (missing: *n* = 2)
Number of self‐reported physical (and not‐elsewhere reported neuropsychiatric conditions), Md (25th percentile, 75th percentile)	1 (0, 2), min–max: 0–9
Treatment history	
Received during depression treatment history	
Drug treatment	278 (missing: *n* = 5)
Psychotherapy or talk therapy	238 (missing: *n* = 7)
Family therapy or couple therapy	57 (missing: *n* = 8)
Electroconvulsive therapy (ECT)	5 (missing: *n* = 5)
Bright light therapy	13 (missing: *n* = 4)
Music therapy	5 (missing: *n* = 5)
Art therapy	6 (missing: *n* = 4)
Exercise therapy	4 (missing: *n* = 4)
Natural medicines	16 (missing: *n* = 4)
Hypnosis therapy	1 (missing: *n* = 4)
Lifestyle guidance (frequency)	77 (missing: *n* = 6)
Duration of depressive episode (months): Md (25th percentile, 75th percentile)	12 (6, 26), min–max: 1–216 (missing: *n* = 9)
Number of depressive episodes during lifetime: Md (25th percentile, 75th percentile)	2 (1, 3), min–max: 1–12 (missing: *n* = 7)
Clinical interviews	
Montgomery–Åsberg Depression Rating Scale (MADRS): M (SD)	21.38 (6.04), min–max: 8–37 (missing: *n* = 0)
Diagnostic Interview for Atypical Depression (DIAD)	
Meets atypical depression features criteria	105 (missing: *n* = 1)
Meets DSM‐IV criteria for melancholic features	60 (missing: *n* = 1)
Meets atypical features criteria and does not meet criteria for melancholic features (frequency)	85 (missing: *n* = 2)
Global Assessment of Functioning (GAF): Md (25th percentile, 75th percentile)	52 (50, 58), min–max: 44–80 (missing: *n* = 0)
Clinical scales and measures	
Beck Depression Inventory (BDI): M (SD)	22.26 (9.66), min–max: 0–46 (missing: *n* = 8)
Sense of Coherence Scale (SOC): M (SD)	
Total score	46.89 (12.37), min–max: 21–84 (missing: *n* = 5)
Comprehensibility	17.23 (5.67), min–max: 6–33 (missing: *n* = 5)
Manageability	14.86 (4.54), min–max: 4–26 (missing: *n* = 4)
Meaningfulness	14.81 (4.71), min–max: 4–27 (missing: *n* = 4)
15‐D Questionnaire: M (SD)	0.7645 (0.0919), min–max: 0.4054–0.9815 (missing: *n* = 2)
Cohen Perceived Stress Scale (PSS10): M (SD)	22.77 (6.17), min–max: 2–36 (missing: *n* = 7)
Life Satisfaction Scale (LS‐4): M (SD)	14.09 (3.47), min–max: 5–20 (missing: *n* = 4)
Life Orientation Test‐Revised (LOT‐R) 6‐item version: M (SD)	10.05 (4.73), min–max: 0–21 (missing: *n* = 6)
Young Schema Questionnaire (YSQ‐S2‐extended): M (SD)	
Disconnection & rejection domain score	14.55 (5.20), min–max: 5.4–28.0 (missing: *n* = 6)
Impaired autonomy & performance domain score	9.46 (3.16), min–max: 4.0–19.0 (missing: *n* = 10)
Impaired limits domain score	4.84 (1.56), min–max: 2.0–11.0 (missing: *n* = 5)
Other‐directedness domain score	9.79 (2.30), min–max: 3.6–17.2 (missing: *n* = 7)
Overvigilance & inhibition domain score	13.18 (3.50), min–max: 4.6–21.6 (missing: *n* = 6)
Clinical Outcomes in Routine Evaluation Outcome Measure (CORE‐OM) Total raw score: M (SD)	54.46 (16.21), min–max: 7–105 (missing: *n* = 4)
Toronto Alexithymia Scale (TAS‐20): M (SD)	
Total score	53.67 (11.0), min–max: 22–81 (missing: *n* = 4)
Difficulty in identifying feelings factor score	19.91 (5.65), min–max: 7–33 (missing: *n* = 4)
Difficulty in describing feelings to others factor score	14.37 (4.56), min–max: 5–24 (missing: *n* = 4)
Externally oriented thinking factor score	19.38 (4.40), min–max: 8–35 (missing: *n* = 4)
Brief Resilient Coping Scale (BRCS): M (SD)	11.69 (2.91), min–max: 4–20 (missing: *n* = 4)
The Trauma and Distress Scale (TADS): Md (25th percentile, 75th percentile)	
Total score	3.6 (2.0, 6.2), min–max: 0–15.4 (missing: *n* = 6)
Emotional abuse factor score	5.0 (2.0, 9.0), min–max: 0–19.0 (missing: *n* = 6)
Physical abuse factor score	1.0 (0, 3.0), min–max: 0–20 (missing: *n* = 4)
Sexual abuse factor score	0 (0, 1.0), min–max: 0–17 (missing: *n* = 4)
Emotional neglect factor score	8.0 (5.0, 12.0), min–max: 0–20 (missing: *n* = 4)
Physical neglect factor score	4.0 (2.0, 7.0), min–max: 0–16 (missing: *n* = 4)
Symptom Checklist‐90 (SCL‐90) Total score: M (SD)	1.26 (0.56), min–max: 0.04–3.32 (missing: *n* = 3)
Blood samples	
Fasting plasma blood glucose (mmol/L), Md (25th percentile, 75th percentile)	5.4 (5.1, 5.8), min–max: 4.0–27.1 (missing: *n* = 2)
Fasting plasma triglycerides (mmol/L), Md (25th percentile, 75th percentile)	1.04 (0.72, 1.50), min–max: 0.33–5.91 (missing: *n* = 1)
Total cholesterol (mmol/L), M (SD)	4.76 (0.95), min–max: 2.6–8.6 (missing: *n* = 2)
Low‐density lipoprotein (LDL) (mmol/L), M (SD)	3.0 (0.95), min–max: 0.9–6.6 (missing: *n* = 1)
High‐density lipoprotein (HDL) (mmol/L), M (SD)	1.59 (0.44), min–max: 0.71–3.02 (missing: *n* = 1)
Plasma albumin (g/L), M (SD)	40.94 (4.07), min–max: 29.0–64.0 (missing: *n* = 2)
Serum high‐sensitivity C‐reactive protein (mg/L), Md (25th percentile, 75th percentile)	0.9 (0.4, 2.83), min–max: 0.0–30.3 (missing: *n* = 17)
Erythrocyte sedimentation rate (mm/h), Md (25th percentile, 75th percentile)	5.0 (2.0, 8.0), min–max: 2.0–37.0 (missing: *n* = 2)
Serum 25‐hydroxyvitamin D (nmol/L), M (SD)	60.96 (25.8), min–max: 14.0–183.0 (missing: *n* = 2)
Red blood cell folate (nmol/L), M (SD)	1825.91 (422.06), min–max: 1148.0–4696.0 (missing: *n* = 5)
Plasma vitamin B12 (pg/mL), M (SD)	414.78 (191.91), min–max: 88.0–1414.0 (missing: *n* = 1)
Fasting parathyroid hormone (pg/mL), M (SD)	49.92 (21.13), min–max: 5.0–183.0 (missing: *n* = 5)
Plasma calcium (mmol/L), M (SD)	2.33 (0.09), min–max: 2.09–2.89 (missing: *n* = 2)

